**3.4.2 Secondary Endpoints**

1) Complete healing of small intestinal mucosal breaks

2) Improving the Lewis score

3) Improving hemoglobin and albumin levels

4) Safety evaluation

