Meanwhile, another problem that arose is the presence of cases in which gastrointestinal bleeding other than gastric, duodenal, and large intestinal bleeding is suspected, and the number of patients in 1999 was reported to be as many as 45,000 based on the estimation of the incidence of peptic ulcer (bleeding) of unknown site performed by Japanese the Ministry of Health, Labour and Welfare once every 3 years. Endoscopy through the oral and transanal routes has generally been performed; however, diagnosis in the small intestine, a long organ with a length of approximately 7 m, has been inadequate. Recently, the development of capsule endoscopy and balloon endoscopy has allowed the observation of the entire small intestine, enabling the detection of small intestinal diseases such as small intestinal bleeding and small intestinal tumors.7-9 In Spain, an epidemiologic study in >30,000 subjects has been conducted, and death due to lower gastrointestinal disease was reported in 8.8% in 2005, which was a significant increase compared with the 5.5% rate in 2001. A recent increase in patients taking LDA has been pointed out as one of the causes.10 This is considered to be because of the difficulty of antisecretory drugs to act on the small intestine.

In our previous study, a significant improvement effect was observed after an 8-week administration of misoprostol (prostaglandin preparation) for small intestinal damage (redness and mucosal break) in patients receiving long-term aspirin therapy.11 This finding suggests the possibility that prostaglandin preparations may act on the small intestine. However, because misoprostol is associated with a high incidence of adverse reactions, such as diarrhea, candidate drugs in addition to misoprostol need to be further investigated.

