**3.1.1 Inclusion Criteria**

Subjects who meet the following conditions will be registered into this study:

1. Subjects who provided written consent for participation.
2. Subjects who have been receiving treatment with Bayaspirin (100 mg/day or lower) for at least 3 months, and who are scheduled to continue Bayaspirin for the study period of 8 weeks or longer.
3. Patients with diseases such as ischemic heart disease and ischemic cerebrovascular disease whose conditions are stable.
4. Subjects aged 20 years or older.
5. Subjects of both sexes.
6. Subjects with small intestinal damage detected with capsule endoscopy.

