**3.1.3 Handling of Patients**

1) The investigator will provide an adequate explanation about participation in this study, and will obtain consent from participants.

2) If some mucosal damage is observed on small intestinal endoscopy, the investigator will confirm that the subject satisfies the inclusion criteria and does not meet the exclusion criteria, and will register the subject into the study.

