**3.3.6 Contents and Schedule of Examination**

**Study design**

**Group A**

**(n=15)**

**Group B**

**(n=30)**

**Ｃａｐｓｕｌｅ　ｅｎｄｏｓｃｏｐｙ**

**pre**

**Ｂｌｏｏｄ　ｔｅｓｔ**

**Objective symptom**

**4 weeks**

**8 weeks**

**Ｓｕｂｊｅｃｔｉｖｅ　ｓｙｍｐｔｏｍ**

**3.3.6 Observation Items**

Subject background: Specified at registration

ID assigned by randomization, date of birth, sex, height, body weight, body mass index, drinking history (years), smoking history (years), underlying disease, complications, and used drugs (drug name, dose, and period of use)

Treatment compliance: Status of the administration of the drug

Hematology: Before administration, after administration (4 weeks), and at the completion of treatment (8 weeks)

Red blood cells (104/μL), white blood cells (104/μL), hemoglobin (g/dL), albumin (g/dL), hematocrit (%), total protein (g/dL), glutamic oxaloacetic transaminase (IU/L), glutamic pyruvic transaminase (IU/L), blood urea nitrogen (mg/dL), creatinine (g/day), iron (μg/dL), and C-reactive protein (μg/dL)

Subjective and objective symptoms: Before administration, after administration (4 weeks), and at the completion of treatment (8 weeks)

Subjective symptoms: Epigastric pain, abdominal distension, anorexia, heartburn, stomach heaviness, nausea, vomiting, belching, etc.

Objective symptoms: Epigastric tenderness, hematemesis, melena, etc.

Small intestinal endoscopy: Before administration and at the completion of treatment (8 weeks)

Stool frequency, abdominal symptoms, etc. (after examination; abdominal symptoms and capsule excretion symptoms will be confirmed)

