**3.4 Evaluation Criteria**

**3.4.1 Primary Endpoint**

Decreasing the number of small intestinal mucosal breaks

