**3.7.1.2 Method of analysis of the primary and secondary endpoints**

The Wilcoxon signed-rank test (for continuous data) or McNemar test (for ordinal data) was used for comparisons of data between baseline and 8 weeks. Differences with P-values <0.05 were considered significant.

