**3.7.1.4 Sample size**

Sample size was estimated based on a previous study showing that the complete healing rate of LDA-induced mucosal breaks was 58% in patients who took misoprostol, a PGE1 analog, for 8 weeks. The following assumptions were made for sample size calculation: (1) the wound-healing effect of a triple dose of rebamipide was equal to that of misoprostol; (2) the complete healing rates in the placebo and rebamipide groups were 20% and 58%, respectively; (3) 10% of patients in each group will either drop out or have unsatisfactory follow-up VCE images. We calculated that at least 30 patients were needed in the rebamipide group to give the study 90% power at a 5% significance level by a test of proportions.

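### Section 3.7.1.2 tests complete healing only against baseline, so it counts non-drug healing as an effect, and it makes no use of the baseline break count

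*Protocol*

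**What the plan says.** The primary endpoint (3.4.1) is "Decreasing the number of small intestinal mucosal breaks". The first secondary endpoint (3.4.2) is "Complete healing of small intestinal mucosal breaks"; the protocol does not define it further, and zero breaks on the 8-week capsule is the natural reading. Section 3.3.6 schedules capsule endoscopy once before treatment and once at 8 weeks.

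For these endpoints section 3.7.1.2 gives one method: "The Wilcoxon signed-rank test (for continuous data) or McNemar test (for ordinal data) was used for comparisons of data between baseline and 8 weeks". No comparison of rebamipide with placebo appears there. Tests between the groups are named in 3.7.1.1, for patient characteristics.

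The sample size (3.7.1.4) is nevertheless a two-group calculation on healing. It assumes that "the complete healing rates in the placebo and rebamipide groups were 20% and 58%, respectively", with 10% loss per group, and refers to a test of proportions. The design diagram shows 15 patients in group A (placebo) and 30 in group B (rebamipide). Allocation is by minimisation, with factors not named (3.3.5).

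Entry requires "Subjects with small intestinal damage detected with capsule endoscopy" (3.1.1), and registration follows "If some mucosal damage is observed on small intestinal endoscopy" (3.1.3). Neither sets a minimum number of breaks.

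**The concern.** The trial is randomised and placebo-controlled so that healing which would have happened anyway can be subtracted. A baseline-to-8-week test does not subtract it. The protocol itself expects one placebo patient in five to heal completely, so a significant paired test in the rebamipide arm would be weak evidence about the drug. The same logic applies to the signed-rank test on the number of breaks.

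A second, smaller matter is the baseline number of breaks. A patient with one break plausibly reaches zero more easily than a patient with ten, yet the named tests treat both alike. The count is already collected as the baseline of the primary endpoint. In a trial of about 45 patients, leaving it out of the healing comparison may lose precision, and a chance difference in break count between the arms stays uncorrected.

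**Working it through.** **1. The protocol's own figure.** Inputs from 3.7.1.4: 20% v 58%, power 90%, alpha 5%, loss 10%. With pooled variance, 1:1 allocation and a one-sided test, the mean proportion is (0.20 + 0.58)/2 = 0.39, and

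n = [1.645 × √(2 × 0.39 × 0.61) + 1.282 × √(0.20 × 0.80 + 0.58 × 0.42)]² / 0.38² ≈ 26.3, so 27 per arm, and 27/0.9 = 30.

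The stated 30 is reproduced, but as one-sided and 1:1 (two-sided 1:1 gives 37). What matters here is that the calculation compares two arms. The analysis section does not.

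**2. When McNemar's test is significant.** Suppose every patient in an arm has a break at entry, so none is healed at baseline. All discordant pairs then go one way. With k healed patients:
- Exact two-sided P = 2 × 0.5^k. For k = 5 this is 0.0625 and for k = 6 it is 0.031, so 6 healings suffice.
- Uncorrected chi-square = k²/k = k, which exceeds 3.84 from k = 4.

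**3. How often that happens without a drug effect.** Let both arms heal at the protocol's 20%, with the number healed binomial:

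| Arm | Exact, P(X ≥ 6) | Chi-square, P(X ≥ 4) |
|---|---|---|
| 30 (rebamipide, planned) | 57% | 88% |
| 27 (after 10% loss) | 46% | 82% |
| 15 (placebo, planned) | 6% | 35% |

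The larger arm crosses the line far more often at the same healing rate. With independent arms, the pattern of significance on rebamipide but not on placebo arises by arm size alone with probability 0.572 × (1 − 0.061) = 0.54 (exact) or 0.877 × (1 − 0.352) = 0.57 (chi-square).

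**4. The same situation compared between arms.** Fisher's exact test at 15 v 30 with a common healing rate has a type I error of 3.0% at 20% healing, 3.1% at 40% and 2.9% at 50%. Non-drug healing does not create a false difference.

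**5. Chance imbalance in break count.** Evaluable arms are 30 × 0.9 = 27 and 15 × 0.9 = 13.5, taken as 14. Assume a share p of patients has one or two breaks, and simple randomisation. The standard deviation of the difference in that share is √[p(1 − p)(1/27 + 1/14)]: 0.151 for p = 0.3 and 0.165 for p = 0.5. A difference of 15 points or more then has probability about 32% to 36% by the normal approximation. Minimisation on break count would lower this, but the factors are not stated.

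**6. Power from using the baseline count.** This was simulated at 27 v 14 with 58% v 20% healing. The assumptions were gamma-Poisson lesion loads with mean 2, 4 or 8, each break seen with probability 0.8, and critical values calibrated under the null. Adding log baseline count gained:
- about 4 to 10 points if breaks heal independently (repeat runs gave 1 to 13);
- 0 to 5 points at a within-patient correlation of 0.3;
- 1 to 3 points at 0.6, within simulation error;
- about none at 0.8.

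**The case against.** The strongest reply has three parts.

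**The comparison may be in the statistical analysis plan.** Covariates and models are commonly left to that document, which is not at hand, and the sample-size section shows that a between-arm test of healing was in mind. This stands for the covariate taken alone. It does not stand for the test, because 3.7.1.2 fixes a method for the endpoints and that method is paired.

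**The endpoint is secondary and the trial is a declared pilot.** The number of breaks is primary and keeps the information that an all-or-nothing endpoint discards. That limits the weight of the point. Healing is still the endpoint on which the trial is sized.

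**The benefit of adjustment is uncertain.** The gain depends on how breaks heal within a patient, on which the protocol gives no data. This is right, and the range above reflects it.

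A reader might also infer something stronger: that entry sits one lesion away from response, so that patients with one or two breaks become responders without a drug effect and distort the healing result. The protocol does not support that. It sets no one-break threshold, and its introduction describes damage as covering redness as well as breaks, so a patient with no break is not excluded. Missed or spontaneously closed breaks occur in both blinded arms and do not bias the contrast. Under assumed detection of 0.7 to 0.9 per break, reading noise alone would turn 1% to 11% of patients with a seen break into healed ones, less than the 20% already allowed on placebo. Adjusting for baseline count would not correct a missed break in any case.

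**Conclusion.** The point holds in two parts of unequal weight.

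The main part is that 3.7.1.2 names only baseline-to-8-week tests, which cannot separate drug from non-drug healing. Its size, 57% to 88% for a 30-patient arm, uses the protocol's own 20%. It further assumes that McNemar's test is applied within each arm, which 3.7.1.2 does not say, and that every patient has a break at entry. If the test were run on both arms together, it would carry no information about the drug.

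The lesser part is that the baseline number of breaks goes unused. This is a question of efficiency and chance imbalance, not of validity. The possible gain runs from about 4 to 10 points of power down to nearly nothing, and it rests wholly on assumed lesion loads, detection and healing correlation. Adjustment would not close any gap to the stated 90% power.

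**What to change.** In 3.7.1.2, replace the baseline-to-8-week test for complete healing with a comparison of rebamipide and placebo:
- **Population:** patients with at least one mucosal break at baseline. The logarithm of the count is undefined at zero, and a patient without breaks has nothing to heal.
- **Model:** penalised (Firth) logistic regression with treatment and log(baseline number of breaks). Alternatively, use an exact or permutation P value that respects the minimisation procedure.
- **Presentation:** crude healing proportions by arm beside the adjusted result, and healing shown descriptively by baseline count (for example 1 to 2 v 3 or more). Baseline-to-8-week changes may stay as description.

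The cost is a few lines of text and a little analysis work. No further capsule, visit or reading is needed, because the baseline count is already recorded. There are two small downsides. The adjusted odds ratio is conditional on baseline count, so it will not match the crude one. Patients with no break at baseline do not contribute to this endpoint.

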**3.5 Criteria for Study Termination and Dropout of Subjects**

1. Observation down to the cecum is not completed within the capsule endoscopy measurement time (8 h).
2. Adverse reactions judged to be serious, such as peptic ulcer, gastrointestinal bleeding, and perforation, develop.
3. Drugs described in the exclusion criteria are added.
4. The subject requests to discontinue study participation, and the investigator or principal investigator judges a discontinuation to be appropriate.
5. Compliance with treatment with the test drug during the study is <85%.

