**3.2 Study Design**

Classification based on the method of administration of the drug: A randomized, double-blind, placebo-controlled study.

Classification based on the contents of the study: A study to explore drug effect.

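### Section 3.5 merges stopping study drug with leaving the study, so post-randomisation losses can bias the comparison in either direction

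*Protocol*

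**What the plan says.** The trial is described in section 3.2 as "A randomized, double-blind, placebo-controlled study". Section 3.5 is headed "Criteria for Study Termination and Dropout of Subjects" and gives one list with no distinction between coming off study drug and leaving the study. Three of its five items matter here:

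- "Observation down to the cecum is not completed within the capsule endoscopy measurement time (8 h"). No visit is named.
- "Adverse reactions judged to be serious, such as peptic ulcer, gastrointestinal bleeding, and perforation, develop".
- "Compliance with treatment with the test drug during the study is <85" per cent.

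The outcome is read from the capsule, and section 3.3.6 (Observation Items) schedules it twice: "Small intestinal endoscopy: Before administration and at the completion of treatment (8 weeks"). The primary endpoint (3.4.1) is "Decreasing the number of small intestinal mucosal breaks". Complete healing, hemoglobin and albumin are secondary (3.4.2). Section 3.7.1.2 analyses the endpoints by paired tests of baseline against week 8. Section 3.7.1.4 assumes that "10% of patients in each group will either drop out or have unsatisfactory follow-up VCE images". No section says that a patient who meets a 3.5 criterion is still assessed at week 8 or stays in the comparison.

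**The concern.** Randomisation makes the two groups comparable at the start. That protection weakens when patients leave because of something that happened afterwards and that may depend on the assigned drug or on how the patient is doing.

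All three events can be of that kind. Adverse reactions and compliance can differ by drug. Ulcer and gastrointestinal bleeding lie close to the outcome and to the hemoglobin endpoint. An incomplete follow-up capsule removes the outcome itself, although a partial recording that already shows a break proves that the patient has not healed.

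Because there are only two capsule studies, a patient who leaves before week 8 has no endpoint value. A later definition of analysis sets cannot recover it. With 15 patients planned on placebo, a few losses are enough to shift the estimate.

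**Working it through.** **Inputs.** Healing 20% on placebo and 58% on rebamipide, 10% loss per group, 90% power, 5% level (section 3.7.1.4). Group sizes 15 and 30 (section 3.3.6, Contents and Schedule of Examination). Nine tablets a day for 8 weeks (section 3.3.5). Loss of 20% and any split of losses by arm are assumptions.

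**1. The plan's own figure.** With a one-sided 5% test and equal groups, n = [1.645·√(2·0.39·0.61) + 1.282·√(0.20·0.80 + 0.58·0.42)]² / 0.38² = 26.3, so 27. Then 27/0.9 = 30, the stated number. (A two-sided test with equal groups gives 33, or 37 after inflation.) The 30 therefore stands for 27 evaluable patients: the plan budgets dropouts and poor follow-up images as lost.

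**2. How easily the compliance item is met.** 9 × 56 = 504 tablets. Missing 76 leaves 428/504 = 84.9%, which is about 8.4 days' worth of tablets. As compliance is judged over the whole study, even a patient with a complete week-8 capsule can be a dropout.

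**3. What the retained patients can tell us.** Let a share d be lost in each arm, with 58% v 20% healed among the rest. The all-randomised difference lies between these bounds:

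- Lower (lost rebamipide patients all unhealed, lost placebo patients all healed): 0.58(1−d) − [0.20(1−d) + d]
- Upper (the reverse): [0.58(1−d) + d] − 0.20(1−d)

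| d | Lower | Upper | All lost counted as not healed |
|---|---|---|---|
| 10% | 0.522 − 0.280 = 24.2 points | 0.622 − 0.180 = 44.2 points | 0.522 − 0.180 = 34.2 points |
| 20% | 0.464 − 0.360 = 10.4 points | 0.664 − 0.160 = 50.4 points | 0.464 − 0.160 = 30.4 points |

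The retained patients show 38 points in every row.

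**4. Direction.** Suppose the true rates are 58% v 20% and all lost patients are non-healers.

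- 10% lost in both arms: 0.58/0.9 − 0.20/0.9 = 64.4% − 22.2% = 42.2 points, an overstatement.
- 10% lost on placebo only: 58% − 22.2% = 35.8 points, an understatement.

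With no drug effect and 20% healing in both arms:

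- Equal loss gives a false difference of 0.
- Loss of 5% on placebo and 20% on rebamipide gives 0.20/0.80 − 0.20/0.95 = 25.0% − 21.1% = 3.9 points.

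**5. Small numbers.** On placebo, 3/15 healed is 20%. Losing two non-healers gives 3/13 = 23%; losing one healer gives 2/14 = 14%.

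**6. Power if the lost 10% count as not healed.** Rates of 18% v 52.2% at 15:30 give a pooled rate of (2.7 + 15.66)/45 = 0.408. Two-sided power by the normal approximation is Φ[(0.342 − 1.96 × 0.1554)/0.1348] = Φ(0.28) = 61%. Analysing only the retained 13.5 and 27 patients at 20% v 58% gives 65%.

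**The case against.** Several counter-arguments have force.

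- **Exclusion from the analysis is not stated.** Section 3.5 speaks of dropout, section 3.7 defines no analysis set, and a statistical analysis plan not shown may define one. Inflating for attrition is routine. A reader might infer that known failures are deleted; the text does not say so. What stands is that section 3.5 is a stated rule that takes patients out of the study, with no provision for outcome follow-up afterwards.
- **The cecum item names no visit.** Reading it as the week-8 capsule is an inference, supported by the mention of follow-up images in section 3.7.1.4. It may also cover the baseline capsule. Sections 3.1.1 and 3.3.5 require damage to be found before randomisation, but completeness to the cecum is not an eligibility item.
- **The ulcer and bleeding item is narrow.** It covers adverse reactions judged serious, that is, events whose relation to study drug cannot be ruled out (3.6.1), not every bleed or ulcer. Both arms take nine tablets a day under blinding, so tablet burden alone does not show that compliance will differ.
- **A full recording matters for a count.** A partial week-8 recording can miss breaks and falsely suggest a decrease. This is a good reason not to treat a partial recording as a full count. It is no reason to lose the patient.
- **The figures concern healing, which is secondary.** The protocol gives no distribution for the break count, so no figure can be computed for the primary endpoint. The mechanism is the same.
- **The trial is a declared pilot.** That lowers the stakes, but it is still randomised and tested at P<0.05.

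**Conclusion.** The point holds as a risk of bias created by a rule in the protocol. Section 3.5 ends study participation for events that can follow randomisation and can relate to treatment or outcome, and section 3.7.1.4 plans for such patients to be lost. The loss can bias the comparison in either direction.

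On the protocol's healing rates, 38 points among those retained is compatible with 24.2 to 44.2 points in all randomised patients at 10% loss per arm, and with 10.4 to 50.4 points at an assumed 20%. These are extreme bounds, not expected values. The actual size depends on loss by arm and on the outcomes of those lost, neither of which the documents give.

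A reader might infer that the drug effect will be overstated, or that a sizeable effect would appear from nothing. The documents support neither. Loss confined to placebo non-healers understates the effect, and equal loss of non-healers with no true effect produces no false difference. Nothing here questions when treatment should be stopped.

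**What to change.** Leave the treatment-stopping rules as they are and change what follows from them:

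- State that meeting a 3.5 criterion does not end outcome follow-up. Obtain the week-8 capsule and blood tests, both already scheduled, in every willing randomised patient for whom the investigator judges the capsule appropriate.
- Analyse all randomised patients as allocated.
- For complete healing (secondary), count as not healed any patient with no usable week-8 recording, or with an incomplete one that shows a break.
- For the break count (primary), fix one rule for missing or incomplete recordings that does not read a partial recording as a full count. Assigning the worst rank is one example, and it suits a rank-based test. Add a sensitivity analysis under a different assumption.
- Use the set with at least 85% compliance and a complete capsule only as a sensitivity analysis.
- Say which visit the cecum criterion refers to, and settle completeness of the baseline capsule at eligibility, before randomisation.

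The cost is protocol wording and follow-up of a few more patients at a visit that already exists. The apparent effect may be smaller (34.2 instead of 38 points if the planned 10% count as not healed) and power lower, at about 61% two-sided with 15:30. Counting missing patients as failures also misclassifies any who had in fact healed and weighs more on the arm with more losses, which is why the sensitivity analyses are needed.
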